### Intervention

2.7

We chose a MeDi based on Avocados because of the need to have stronger evidence to support current recommendations and because avocados are widely available and used in many parts of the world more so than olive oil. We chose the low-fat control diet because it is similar to what many clinicians and dietitians still recommend and what patients do to lower cholesterol levels after stroke. We improved it using high-quality complex carbohydrates (whole grains) and fiber content.

The elaboration of diets, the content of the sessions, and written material were made and reviewed by an experienced physician nutritionist specialist and a registered dietitian nutritionist (nutritionist) with experience in Mediterranean and low-fat high-complex diets. The study nutritionist and study nurses underwent initial specific training in all study procedures by the study investigators, and subsequently all study interventions are reviewed in weekly meetings.

As part of our institutional stroke registry in all patients, a MEDAS score is obtained, which is used for randomization. The randomized diet is notified by an investigator to the study nutritionist after consent is obtained. This study nutritionist is in charge and follows the patients throughout the study.

Anthropometric measurements are performed in person by a study nurse or study nutritionist according to the study schedule (Table 1).

**Table 1 T1:** Schedule of study evaluations.

Evaluation	Baseline	30 d	60 d	90 d
Eligibility	X			
Modified Rankin scale score	X			X
14 item Mediterranean diet questionnaire (MEDAS)	X			X
Written informed consent	X			
Randomization	X			
Secondary prevention medication questionnaire	X			X
Food frequency questionnaire	X			X
24-h food recall questionnaire		X	X	X
Rapid Assessment of Physical activity questionnaire (RAPA)	X			X
Anthropometric measures	X			X
Study blood samples	X			X
Allocated diet administration	X			
Nutritional counseling and dietary reinforcements	X	X	X	X
Questionnaire of AEs and SAEs		X	X	X
Telephone follow-up		X	X	
In person follow-up				X
Trial acceptability questionnaire				X

Several instruments are applied in a timely manner to each patient according to the study schedule outlined in the table. These included a food frequency questionnaire, a 24-hour food recall questionnaire, the Rapid Assessment of Physical Activity questionnaire, questionnaire of adverse events (AE) and serious adverse events (SAE), the MEDAS questionnaire, a structured questionnaire about the acceptability of the trial, a modified Rankin scale score, and a questionnaire about medications being administered, especially lipid lowering.

All patients received dietary counseling by a study nutritionist who explains the characteristics and composition of the allocated diet in an interview. This includes portions sizes, daily quantities, what to include and what to avoid in each diet type. Patients are also provided with detailed written information about typical foods for each dietary pattern, seasonal shopping lists, meal plans, and 14-day recipes. In all cases, the allocated diet starts when the patient is at home and before 1 month of symptom onset. The study nutritionist in charge of the patient is available through telephone during the entire participation period for any extra contact the patient may need. Patients in both intervention arms receive the same intensity of dietary counseling. Each patient receives at least 4 sessions with a study nutritionist during the 3 months of intervention.

In the baseline session, the patient receives nutritional counseling and education according to the randomized diet, applying the instruments as described in the study schedule (Table 1). The usual duration of this session is ±90 minutes. At 30 ± 7 and 60 ± 7 days, telephone follow-up is performed by the same nutritionist who inquiries about the diet pattern, applies the instruments according to the study schedule, and provides specific feedback recommendations and reinforcements on the allocated diet pattern. The usual duration of these sessions is ±30 minutes. At 90 + 14 days, follow-up a closing nutritional session is conducted including the application of the appropriate instruments according to the study schedule (Table 1), and the delivery of dietary recommendations for healthy habits as post-trial care. In this session, 1 of the physician investigators obtains the modified Rankin Score, the details of the medications being taken by the patient and details about any AE or SAE if they occurred. The usual duration of this session in ±45 minutes. Before the pandemic, the baseline and 3 months sessions were carried out in person, scheduling a visit to the hospital by the patient, since March 2020 to date these sessions are mixed: measurements and samples in person and intervention/instruments by video conference. If the patient is unable to answer, the caregiver living with the patient or who oversees cooking and feeding the patient is interviewed.

The diets are standard normocaloric adjusted depending on the nutritional status and physical activity of the patient, but the focus of both diets is on the quality of the food and not the quantity. We anticipate that weight loss may occur in some patients due to improved eating habits and food selection. For each intervention, 3 different daily caloric dietary contributions were made: 1500, 1800, and 2000 calories. The macronutrient distribution of each diet intervention is as follow:

A.Mediterranean diet: 50% total caloric value of carbohydrates, 35% fat (22% MUFA fat, 6% polyunsaturated fatty acids (PUFA) fat, ±10% saturated fat), and 15% protein.B.Low-fat high-quality carbohydrate: 55% carbohydrates, 30% fat (12–14% MUFA fat, 6–8% PUFA fat, ±10% saturated fat), and 15% protein.

Both diets include natural foods, little processed, and naturally low in sodium, and cooking with little added salt and using spices to season meals is reinforced during food education. With these guidelines, it is intended that the patient consumes a maximum of 5 g of salt per day between foods that contains it and the added salt. In both diets, the consumption of oil is daily, and it is recommended to include it raw to dress salads. The MUFA content of the low-fat high-quality carbohydrates is 12% to 14% versus 22% in the Mediterranean diet; therefore, the selection of foods that are included in these minutes corresponds to this calculation. The contribution of olive oil to be used is lower than that in the classical Mediterranean diet and can be replaced by canola oil if the patient does not consume olive oil, and the frequency of foods rich in MUFA (nuts, avocado) and PUFA (fish) is also less than that indicated in the Mediterranean diet. Both diets include complex carbohydrates, that is, from whole grains, fruits, vegetables, legumes, meats, and low-fat dairy products, and very low or no contribution of simple sugars. In patients with diabetes mellitus, the contribution of complex carbohydrates is the same as that in non-diabetic patients. Depending on the pharmacological treatment that the patient has for diabetes mellitus, an adjustment of the number of mealtimes can be made to avoid hypoglycemia if the patient uses sulfonylureas or insulin. The meal plan includes specific recommendations for each diet intervention, as well as a menu divided into 4 meals and a snack during the day with options for 14 days. This menu must be replicated and combined during the 3 months of patient participation.

To maintain diet fidelity with the intervention, in all contacts the study nutritionist emphasizes that the portions and frequencies of food of the diet assigned to the patient are respected, solve specific doubts, and inquire about AE and SAE. The food surveys are analyzed qualitatively and quantitatively by the study nutritionist in charge of carrying them out. The qualitative analysis considers the number of meals per day, fluid intake, and quality of the food consumed, which is compared to each of the diet interventions. The quantitative analysis is carried out by obtaining the ingredients and quantities of each food preparation that the patient consumes, this is then transformed into portions to obtain the intake of calories, carbohydrates, fats, and proteins. This is compared with the requirements of the assigned diet and the % of adequacy is calculated ([intake value/requirement value] × 100). An adequate intake is considered if the macronutrient is in a percentage of adequacy of 90% to 110%. We use as a reference the contributions of nutrients and calories from the “Exchange portions and Chemical Composition of foods of the Chilean food pyramid” National Institute of Food Technologies, 1999 and its update “Food Composition Table” National Institute of Food Technologies, 2018.^[31]^ This information is used to personalize each interview and adjust counselling.

As part of the institutional protocol and Chilean stroke national guidelines, all patients receive appropriate secondary stroke prevention and are discharged with an antithrombotic statin at high doses (usually atorvastatin 80 mg day, a hypotensive, and if necessary, a hypoglycemic drug). The patients are counseled at each study visit to keep their secondary prevention medications according to their treating physician prescriptions.

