### Masking

2.6

Participants and investigators are not masked to the intervention diets; however, outcome assessors of LDL-C and other laboratory results, and data analysts are masked to the diet allocation. Unblinding is not anticipated.

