### Data collection, retention, and follow-up

2.11

Data collection and follow-up assessments are performed by trained study personnel according to the schedule in the table. Patients are encouraged to stay in the study even if they are non-adherent to the assigned intervention diet and complete follow-up assessment. Extra telephone calls are performed by the study nutritionist according to the patient's needs.

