### Feasibility, adherence, and acceptability

2.12

To maintain adherence to and assess the feasibility of the intervention, participants are contacted by telephone at 1 and 2 months after recruitment. The telephone calls are made by study nutritionists to each participant to reinforce the allocated diet and administer a 24-hour diet recall questionnaire. Patients have extra telephone calls and email contacts depending on the individual evaluation of each nutritionist.

To increase adherence, randomized patients are transferred monthly an amount of money equivalent to buying avocado (2 kg per week, including family consumption) or whole grain bread (2 kg per week, including family consumption), according to the allocated diet.

The acceptability of the trial in both groups is assessed with a structured 14-item self-applied (or caregiver) questionnaire performed at the end of follow-up. Items are measured using a 5-point Likert scale.

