### Statistical analyses

2.17

All efficacy analyses will be performed according to the intention-to-treat principle. The primary outcome will be compared between the 2 groups by an analysis of covariance adjusting for baseline measures unbalanced by randomization and with baseline LDL-C and statin use (initial and final doses) as covariables. To account for missing data, multiple imputations using chained equations will be used, assuming randomness. The results will be compared to those with complete data. A sensitivity analysis will be carried out to investigate the robustness of the findings according to adherence to the intervention. Safety analysis will be performed for all patients participating in the study. The number of patients with AEs, the occurrence of specific SAEs, and discontinuation due to SAEs will be tabulated. Binary outcomes, such as AEs, major cardiovascular events (acute myocardial infarction, stroke, or vascular death), or death will be analyzed with the Chi-2 test for independence. Analysis of adherence will be performed in all patients who finalized the study. The proportion of patients who completed the intervention at 3 months will be analyzed using the Chi-2 test for independence. The percentage of adequacy of the diet intervention at 1, 2, and 3 months will be analyzed with generalized linear mixed models for repeated measures. Feasibility assessed as the mean time from symptom onset to intervention will be analyzed using Student's *t* test. Analysis of the acceptability 14-item questionnaire will be performed in all patients completing the follow-up with the Mann–Whitney–Wilcoxon non-parametric test. Exploratory subgroup analyses will be carried out irrespective of whether there is a significant treatment effect on the primary outcome. These analyses will be adjusted for confounders. The following pre-specified subgroup analyses will be performed by adding an interaction term to the models: age (< or ≥ mean) years, sex, education level < or ≥12 years, post-stroke disability (modified Rankin score < or ≥1), physical activity (Rapid Assessment of Physical Activity questionnaire score < or ≥6), MEDAS score (< or ≥ median), dyslipidemia (yes/no), diabetes/insulin resistance (yes/no), BMI (< or ≥25), and BMI (< or ≥30). Per protocol analysis will be performed for the primary and key secondary efficacy outcomes, using the same statistical test as per the intention-to-treat analysis.

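### AE ascertainment is not standardized between arms: unmasked nutritionists also ask about AEs at extra contacts whose number is not fixed, and the Chi-2 comparison in 2.17 does not separate these reports

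*Protocol article*

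**What the plan says.** The protocol article describes two routes by which AEs are solicited.

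- **Scheduled.** Table 1 (section 2.7) has a row "Questionnaire of AEs and SAEs", marked at 30, 60 and 90 days and identical for both arms.
- **At every contact.** The text of 2.7 says that "in all contacts the study nutritionist emphasizes that the portions and frequencies of food" of the assigned diet "are respected, solve specific doubts, and inquire about AE and SAE". Nothing limits this to the scheduled visits.

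The number of contacts is open-ended. Section 2.7 sets a minimum of four sessions and no maximum. Section 2.11 says: "Extra telephone calls are performed by the study nutritionist according to the patient's needs". Section 2.12 says: "Patients have extra telephone calls and email contacts depending on the individual evaluation of each nutritionist".

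The person asking knows the diet. Section 2.6 states: "Participants and investigators are not masked to the intervention diets". Section 2.7 adds: "The randomized diet is notified by an investigator to the study nutritionist after consent is obtained".

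Safety is a secondary objective (1.1.2), measured as AE and SAE frequency by group (2.8.2). For the analysis, 2.17 says: "The number of patients with AEs, the occurrence of specific SAEs, and discontinuation due to SAEs will be tabulated". Binary outcomes, AEs among them, are tested with Chi-2. Neither the source of a report nor the number of contacts enters that comparison.

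**The concern.** The number of times a patient is asked about symptoms is settled after randomization, partly by someone who knows the allocation. The checklist in 2.13 covers bloating, fullness, indigestion and altered bowel habits. These are minor complaints that a patient may mention only when asked, so more asking can mean more patients counted.

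The two diets could plausibly attract different amounts of extra support, for instance if one is harder to follow: 2.7 says that food-survey results are used to tailor the interviews and counselling. The arm contacted more often could then show more patients with minor AEs at the same true symptom rate. If the extra contacts fell in the arm with fewer true symptoms, a real difference could be hidden. At stake is whether a difference in minor AEs, or its absence, can be attributed to the diet.

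**Working it through.** The plan has no figure to reproduce: it gives no AE rate, no count of extra contacts and no power for safety. What follows shows how the mechanism behaves under assumptions. It does not estimate the bias in this trial.

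**Inputs from the protocol**
- 100 patients per arm (2.16).
- Alpha 0.05 (2.17); two-sided is assumed.
- Three scheduled AE inquiries per patient in each arm (Table 1).

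**Assumptions**
- No true diet effect.
- Each inquiry independently brings out a reportable AE with probability p = 5%, 10% or 20%.
- One arm has 1 or 2 extra inquiries per patient, the other none.

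**Step 1. Patients with at least one recorded AE**, after k inquiries: P = 1 − (1 − p)^k. At p = 10%, three inquiries give 1 − 0.9³ = 27.1% and five give 1 − 0.9⁵ = 41.0%.

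**Step 2. Chance of a significant difference**, normal approximation: Φ[(d − 1.96·se0)/se1]. Here d is the difference in proportions, se0 the standard error from the pooled proportion and se1 the standard error from the separate proportions. At p = 10%, 3 against 5 inquiries:
- d = 0.4095 − 0.2710 = 0.1385
- pooled proportion = 0.3403; se0 = √(0.3403 × 0.6597 × 2/100) = 0.0670
- se1 = √(0.2710 × 0.7290/100 + 0.4095 × 0.5905/100) = 0.0663
- (0.1385 − 1.96 × 0.0670)/0.0663 ≈ 0.11, so the chance is about 54%

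**Step 3. Allow for recovery.** The questionnaires at 30, 60 and 90 days will record part of what an extra call finds. If they miss a fraction r of it, the arm with two extra inquiries has P = 1 − (1 − p)³(1 − rp)². At p = 10% and r = 0.5 this is 1 − 0.729 × 0.9025 = 34.2%.

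**Results** (100 per arm; the arm without extra contacts is in the second column; the other cells give recorded AE proportion in the extra-contact arm / chance of a false significant difference)

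| p | No extra | 1 extra | 2 extra | 2 extra, half recovered | 2 extra, 75% recovered |
|---|---|---|---|---|---|
| 5% | 14.3% | 18.5% / 13% | 22.6% / 33% | 18.5% / 12% | 16.4% / 6% |
| 10% | 27.1% | 34.4% / 20% | 41.0% / 54% | 34.2% / 19% | 30.7% / 8% |
| 20% | 48.8% | 59.0% / 30% | 67.2% / 76% | 58.5% / 28% | 53.8% / 10% |

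The formula counts only rejections in the direction of the extra contacts, so it slightly understates the two-sided rate when the difference is small.

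**Step 4. Two checks.** With equal contacts in both arms the recorded proportions are equal and the rate is the nominal 5%. With only the three scheduled questionnaires counted, the proportions are again equal (14.3%, 27.1% or 48.8% in both arms) and the rate is 5%.

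**The case against.** The strongest reply is that no bias has been shown. Bias between arms needs a different number of extra contacts, and nothing in the article says there will be one. Section 2.7 states that both arms get counselling of equal intensity. That stands as an intention, but it does not fix the number of extra contacts, which 2.11 and 2.12 leave open.

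A reader might go further and infer that the AE comparison is biased by construction, or that AE frequency will track contacts rather than diet. The documents do not support that: contacts would add to any diet effect, and would distort the comparison only if they differ by arm.

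Four further points:

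- **Safeguards.** Collection runs from consent to the final visit, the same questionnaire is used three times in both arms, a physician investigator asks about AEs at the closing session, and an independent investigator adjudicates. The first three reduce the problem, and because patients rather than events are counted, repeat reports add nothing. Adjudication does not help here, since it acts only on events already reported.
- **Extreme assumptions.** Giving two extra inquiries to every patient in one arm, none in the other, with no recovery, is a worst case. This stands; the two right-hand columns of the table are the more cautious reading.
- **A restricted analysis can mislead too.** Patients may call because of diet-related symptoms. Dropping what those calls reveal could hide a real effect. This stands, and it is why the all-source comparison should remain.
- **Level of detail.** Source coding often sits in a full protocol or SAP. But the article itself states the ascertainment rule, the outcome and the test, and the weakness lies in their combination. A later document cannot separate sources that were not recorded.

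**Conclusion.** The point holds in a conditional form. Soliciting AEs at every contact, leaving the number of contacts open to patient need and to an unmasked nutritionist, and comparing AEs by arm without regard to source together leave ascertainment unstandardized. If extra contacts differ by arm, the Chi-2 comparison of patients with minor AEs can show a difference that the diet did not cause.

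The size cannot be derived from the documents. With p of 10% to 20% and two extra inquiries in one arm only, the false-positive rate would be about 54% to 76% with no recovery, 19% to 28% with half recovered and 8% to 10% with 75% recovered, against a nominal 5%. All of these rest on assumed rates, independent inquiries and a one-sided allocation of extra contacts.

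The scope is narrow: mainly minor, solicited symptoms within a secondary outcome. Deaths and major cardiovascular events depend little on how often a patient is called, and LDL-C is not affected by this route.

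**What to change.** In 2.17:

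1. Keep the all-source AE comparison.
2. Add a pre-specified between-arm comparison of non-serious AEs restricted to those recorded on the scheduled 30-, 60- and 90-day questionnaires. An event first raised in an extra call counts if it is recorded again there.
3. Report the number of extra contacts by arm, and tabulate separately by arm the AEs known only from extra contacts.
4. State that a conclusion on minor AEs is drawn from the all-source comparison only if it agrees with the scheduled-only one.
5. Keep all SAEs, deaths and cardiovascular events in the comparison whatever their source.

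The cost is a few sentences, one extra table and a note of the source of each AE; the scheduled questionnaires are already part of the design. The limitation is timing. Randomization began in August 2018 on paper case report forms, so source and contact counts may be incomplete for patients already followed up. The report should say how many are affected.

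### Percentage of adequacy separates the two diets only through total fat, leaves out MUFA, and says little about adherence if the raw percentage is modelled

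*Protocol article*

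**What the plan says.** Section 2.7 (Intervention) sets the Mediterranean diet at "50% total caloric value of carbohydrates, 35% fat (22% MUFA fat, 6% polyunsaturated fatty acids (PUFA) fat, ±10% saturated fat), and 15% protein" and the control diet at "55% carbohydrates, 30% fat (12–14% MUFA fat, 6–8% PUFA fat, ±10% saturated fat), and 15% protein". The calorie plans are common to both arms: "3 different daily caloric dietary contributions were made: 1500, 1800, and 2000 calories". The contrast on which foods were selected is stated separately: "The MUFA content of the low-fat high-quality carbohydrates is 12% to 14% versus 22% in the Mediterranean diet".

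The same section turns each recalled food into portions "to obtain the intake of calories, carbohydrates, fats, and proteins", divides intake by the requirement of the assigned diet, and multiplies by 100. It then gives the band: "An adequate intake is considered if the macronutrient is in a percentage of adequacy of 90% to 110" percent. No fatty-acid fraction and no avocado or olive-oil item is among the scored components.

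Section 2.8.2 makes this percentage at 30, 60 and 90 days an adherence outcome, together with the median MEDAS score at the end of follow-up. Section 2.17 states: "The percentage of adequacy of the diet intervention at 1, 2, and 3 months will be analyzed with generalized linear mixed models". It names neither the macronutrient nor whether the response is the percentage or the in-band indicator. It also plans a sensitivity analysis by adherence, without saying which adherence measure is meant.

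**The concern.** An adherence score for a two-diet trial should read high for the assigned diet and low for the other one. Here protein and calories are the same by design, and carbohydrate and fat differ by 5 points of energy each, which is close to the width of a ±10% band. The component on which the diets are far apart is not scored.

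The score is also two-sided: 100 is the target, and 80 and 120 are both failures. A group mean near 100 is therefore compatible with good adherence or with poor adherence in both directions.

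At stake is how far a secondary outcome can be interpreted. If LDL-C does not differ between arms, readers will ask whether the diets were actually eaten differently, and this score would contribute little to the answer.

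**Working it through.** The protocol gives no operating figure for this measure, so there is nothing to reproduce. The check applies its formula, 100 × intake / requirement with band 90–110%, to its own targets at equal calories.

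**Step 1. Exact crossover.**

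| Component | Mediterranean target | Control target | Control diet scored as Mediterranean | Mediterranean diet scored as control |
|---|---|---|---|---|
| Calories | equal | equal | 100% | 100% |
| Carbohydrate | 50 | 55 | 55/50 = 110.0% (on the limit) | 50/55 = 90.9% |
| Protein | 15 | 15 | 100% | 100% |
| Fat | 35 | 30 | 30/35 = 85.7% | 35/30 = 116.7% |

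Three components rate a complete crossover as adequate, taking the 110% limit as included. Fat alone flags it, by 4.3 and 6.7 points. The mean of the four percentages is 98.9% in one direction and 101.9% in the other.

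**Step 2. Halfway diet, 52.5/32.5/15.**
- Scored as Mediterranean: 52.5/50 = 105.0%, 32.5/35 = 92.9%, 15/15 = 100%.
- Scored as control: 52.5/55 = 95.5%, 32.5/30 = 108.3%, 15/15 = 100%.

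It is adequate on every component in both arms. The fat bands are 31.5–38.5% and 27.0–33.0% of energy, overlapping at 31.5–33.0%. The carbohydrate bands are 45.0–55.0% and 49.5–60.5%, overlapping at 49.5–55.0%. On a 0.1-point grid of equal-calorie compositions, 496 of the 2,201 adequate for the Mediterranean diet (22.5%) and 496 of the 1,891 adequate for the control diet (26.2%) are adequate for both. This describes the bands. It does not predict what patients eat.

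**Step 3. MUFA.** A Mediterranean-arm patient at 50/35/15 with MUFA at the control level of 12–14% scores 100% on every listed component. On MUFA the same patient would score 12/22 = 55% to 14/22 = 64%. In the other direction, 22/14 = 157% to 22/12 = 183%. The adequate bands would be 0.9 × 22 = 19.8 to 1.1 × 22 = 24.2% of energy, and 0.9 × 12 = 10.8 to 1.1 × 14 = 15.4%. They do not overlap.

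**Step 4. Raw percentage as response.** The spreads here are assumptions, because the article gives none. For a normal distribution centred at 100, the in-band share is 2Φ(10/SD) − 1.

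| SD (points) | Mean | Share within 90–110% |
|---|---|---|
| 5 | 100% | 96% |
| 10 | 100% | 68% |
| 20 | 100% | 38% |
| 30 | 100% | 26% |

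In the extreme case, half the patients at 60% and half at 140% also average 100%, with nobody in band.

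**Step 5. Fat fractions.** Mediterranean: 22 + 6 + about 10 = about 38%, against a stated total of 35%. Control: 12 + 6 + 10 = 28% to 14 + 8 + 10 = 32%, which brackets its stated 30%. A patient eating the Mediterranean fractions as written scores 38/35 = 108.6% on fat, 1.4 points below the upper limit, on the one component that separates the arms.

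**The case against.** A reader might infer that the measure cannot show whether patients followed their diet. The documents do not support that. The band applies to each macronutrient, and the fat component does flag an exact crossover in both directions. No count or composite across the four components is defined, so nothing says that a crossover would be declared adherent overall.

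A reader might also infer that the plan averages the percentage. That is the plain reading of section 2.17, but it is not certain: a generalized linear mixed model can take a binary response, and section 2.7 already defines one. If the in-band indicator is what is planned, the cancelling disappears, while the weak separation and the missing MUFA remain.

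Nor is this the only adherence information. Section 2.8.2 adds MEDAS, section 2.7 a qualitative comparison of food quality with each diet, and Table 1 a food frequency questionnaire at baseline and 90 days. It therefore goes too far to say that a null LDL-C result could not be explained at all, or that this score is what the adherence sensitivity analysis will use. These measures only partly fill the gap, however. MEDAS measures adherence to a Mediterranean diet, not to the control diet, and Table 1 schedules it only at baseline and 90 days. The qualitative review is not a listed outcome and has no stated analysis.

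On the fat figures, the saturated fraction is written as approximate, and the scored item is total fat, so the fractions need not enter the present denominator. That is fair. The fractions and the total still do not agree as printed, and the conflict would matter directly once MUFA is scored.

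**Conclusion.** The point holds in limited form. As specified, percentage of adequacy discriminates between the arms only through total fat, by 4.3 to 6.7 points beyond the band for a complete crossover and not at all for a halfway diet. It omits the contrast on which the diets were built. If the raw percentage is modelled, its mean is uninformative for a two-sided target.

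Steps 1 to 3 rest on the protocol's own targets at equal calories. Step 4 rests on assumed spreads and on reading section 2.17 literally. The components, formula, band and targets are all fixed in the article, so the weak separation is not merely a detail left to a later analysis plan.

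The consequence is confined to a secondary adherence outcome and to any analysis that borrows it. The primary intention-to-treat comparison of LDL-C is unaffected, so this is an inexpensive improvement and not a threat to the main result.

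**What to change.** - **Add MUFA** as a percentage of energy to the scored components, from the recalls at 30, 60 and 90 days, which already record ingredients and quantities. If the composition tables lack fatty-acid values, score intake of avocado and other MUFA-rich foods instead.
- **State the response**, separately for each macronutrient: either the 90–110% indicator in a logistic mixed model, or the absolute deviation from 100%.
- **Reconcile** the Mediterranean fat fractions with the stated total fat before requirements are computed. Which figure stands is for the investigators to settle.
- **Name the measure** that defines adherence in the sensitivity analysis.

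The cost is some recoding of recalls and a few sentences of analysis text, with no new visits or samples. The availability of MUFA values in the tables is an assumption, since the article does not say what they contain.
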